# The systematic early integration of palliative care into multidisciplinary oncology care in the hospital setting (IPAC), a randomized controlled trial: the study protocol

**DOI:** 10.1186/s12913-015-1207-3

**Published:** 2015-12-15

**Keywords:** Palliative care, End-of-life care, Neoplasm, Advanced cancer, Quality of life, Multidisciplinary care, Mood, Informal caregiver, Study protocol

## Abstract

**Background:**

Previous studies in the US and Canada, have shown the positive impact of early palliative care programs for advanced cancer patients on quality of life (QoL) and even survival time. There has been a lack of similar research in Europe. In order to generalize the findings from the US and Canada research on a larger scale, similar studies are needed in different countries with different care settings. The aim of this paper is to describe the research protocol of a randomized controlled trial, situated in Flanders, Belgium, evaluating the effect of systematic early integration of palliative care in standard oncology care.

**Methods/Design:**

A randomized controlled trial will be conducted as follows: 182 patients with advanced cancer will be recruited from the departments of Medical Oncology, Digestive Oncology and Thoracic Oncology of the Ghent University Hospital. The trial will randomize patients to either systematic early integration of palliative care in standard oncology care or standard oncology care alone. Patients and informal caregivers will be asked to fill out questionnaires on QoL, mood, illness understanding and satisfaction with care at baseline, 12 weeks and every six weeks thereafter. Other outcome measures are end-of-life care decisions and overall survival time.

**Discussion:**

This trial will be the first randomized controlled trial in the Belgian health care setting to evaluate the effect of systematic early integration of palliative care for advanced cancer patients. The results will enable us to evaluate whether systematic early integration of palliative care has positive effects on QoL, mood and patient illness-understanding and which components of the intervention contribute to these effects.

**Trial registration:**

Clinicaltrials.gov Identifier: NCT01865396, registered 24^th^ of May, 2013.

**Electronic supplementary material:**

The online version of this article (doi:10.1186/s12913-015-1207-3) contains supplementary material, which is available to authorized users.

## Background

Patients with advanced and incurable cancer typically suffer from a multitude of severe symptoms, which often appear to be under-diagnosed. According to a European multicentre study, symptom intensity is underestimated in one in ten patients, with variations between cancer diagnoses [1]. This underestimation can be explained by a lack of expert knowledge in symptom management, limited time to tend to patients and a strong orientation among health care providers towards cure or life-prolongation rather than quality of life, leading to lack of therapeutic pertinacity [2]. There is evidence that all these problems can be tackled by early implementation of palliative care programs (PCPs) in standard oncological treatment [3–5]. Results from recent randomised controlled trials (RCTs) have demonstrated a positive impact on quality of life of PCP. One PCP for advanced cancer patients, situated in the US, consisted of a phone-based psycho-educational intervention led by a palliative care advanced practice-nurse. The RCT study of this intervention demonstrated positive effects on quality of life and to lower symptom intensity for cancer patients living in a rural setting [6]. Another RCT study, performed in Canada, implemented an intervention that consisted of a palliative care consultation by a palliative care physician and a palliative care nurse with advanced cancer patients with phone-based follow-up and a 24-h on-call service. Positive effects were reported four months after baseline for quality of life, symptom severity and satisfaction with care [7, 8]. Considered as a landmark study on integration of palliative care is the RCT study situated in a major university hospital in Boston, US [4, 9, 10] where the early palliative care intervention consisted of consultations with outpatients with metastatic non-small-cell lung cancer by a physician from the palliative care team shortly after diagnosis of advanced cancer and at least monthly thereafter. Patients in the palliative care group had significantly higher quality of life and a longer median survival of 2.8 months compared with those who received the standard care alone [4, 10, 11]. These promising results influenced the American Society of Clinical Oncology (ASCO) to support the full integration of palliative care as a routine part of comprehensive cancer care in the United States [12]. So far, all published results are from studies that have been conducted in the US and Canada; no results have been published on studies in Europe. Before it can become part of general clinical practice, this early palliative care approach has to be tested in different centres and most importantly in different countries where standard oncology care and/or palliative care may be different from that in the US or Canada.

In Belgium standard oncology care in the hospital is organised on a multidisciplinary model. At the medical level, specialists from different disciplines work closely with each other in diagnosing and treating the patient. At a paramedical level, many resources are devoted to ensuring psychosocial support for cancer patients; every hospital in Belgium with an oncology department has a psychosocial team available for patients and their family carers, consisting of a psychologist, a social worker, a dietician and a nurse specialist. Consultations with the professional caregivers of these teams are free of charge and a first consultation is often organized at the start of treatment. Because of government funding, all hospitals in Flanders, Belgium have a small palliative care team (palliative care nurse 0.5 FTE, palliative care physician 0.5 FTE and palliative care psychologist 0.5 FTE for every 500 hospital beds) available for patients who no longer receive curative treatment or care at the hospital. Palliative care teams are not structurally embedded into the psychosocial team for cancer patients but consultations with them are also free of charge. Patients are mostly seen by a palliative care nurse from the palliative care team [13]. Despite the availability and financial accessibility of palliative care teams, palliative care professionals are only involved in the care of about 60 % of patients with advanced cancer and they are often involved late in the disease trajectory of these patients [14], hence a programme which focuses on systematically providing palliative care early in the disease trajectory of advanced cancer patients is an innovative approach for cancer patients in Flanders, Belgium.

The systematic early integration of palliative care (IPaC) study is the first RCT study on early palliative care for advanced cancer patients to be conducted in the Belgian health care setting. The overall aim of the present paper is to describe the IPaC study protocol.

## Methods

### Study design

This is a phase III randomized controlled trial (RCT) in a hospital setting with advanced cancer patients receiving systematic early integration of palliative care with standard oncology care versus advanced cancer patients receiving standard oncology care alone. Study participants will be randomized in a 1:1 fashion to the intervention arm or standard care arm. Patients will be recruited from the Digestive Oncology, Thoracic Oncology and Medical Oncology departments of the Ghent University Hospital, the second largest hospital in Belgium. These departments have been selected for the trial because almost all cancer patients in the Ghent University Hospital are treated in these departments. Stratification will take place for the treating oncology department (Digestive Oncology, Thoracic Oncology and Medical Oncology) in order to prevent imbalances between groups in factors related to possible differences in standard care [15].

### Study participants

One hundred and eighty two patients with advanced cancer will be recruited by the treating oncologists. Table 1 describes the inclusion and exclusion criteria. Additionally, participants are given the possibility of identifying an important person in their life, either a relative or friend, to be involved in the study as an informal caregiver. The informal caregivers of patients who are randomised to the intervention group may also attend the consultations and hence frequently meet with the palliative care team as opposed to the informal caregivers of the participants in standard care. Table 2 describes the inclusion-criteria for the family carers.

**Table 1 Tab1:** Inclusion and exclusion criteria for the patient

Inclusion-criteria	1. Patients with a solid tumour treated at the Medical Oncology department, Thoracic Oncology department or Digestive Oncology department of the Ghent University Hospital
	2. Patients within 12 weeks of a new diagnosis of illness progression or patients originating from another hospital who are within 12 weeks of receiving first-line treatment
	3. Patients with a life expectancy of approximately one year (assessed by the treating oncologist)
	4. Patients with an Eastern Cooperative Oncology Group (ECOG) performance status of 0, 1 or 2
	5. Patients with the ability to read and respond to questions in Dutch.
Exclusion-criteria	1. Patients under 18 years old
	2. Patients with impaired cognition
	3. Patients with more than one palliative care consultation since the onset of the disease
	4. Patients with one palliative care consultation in the six months before inclusion

**Table 2 Tab2:** Inclusion criteria for the family carer

1. This person should either live with the patient or have in-person contact with him or her at least twice a week.	

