#### Statistical analysis and sample size calculation

To compare baseline characteristics and study outcomes for patients between groups, Fisher’s exact tests, chi-square tests and the independent-samples t-test or the non-parametric equivalent Mann–Whitney *U* will be used. The effect of early palliative care on the primary outcome quality of life will be assessed by multivariate regression analyses adjusting for baseline scores. Survival analysis, i.e. Kaplan-Meier and a Cox proportional hazards model, will be used to examine the effect of systematic early integration of palliative care on the secondary outcome survival from the time of inclusion adjusting for demographic and clinical baseline characteristics. With regard to missing data, we will use the conservative approach of carrying the last observation forward for all missing data.

To detect a significant and meaningful difference in the change of the EORTC QLQ-C30 from baseline to 12 weeks, 118 patients are needed. With the proposed sample size of 59 for the two groups, the study will have a power of 80 % to yield a statistically significant result. This computation assumes a mean score difference of 12 and the common within-group standard deviation is 23.0. A difference of 10 points on the multi-items scales from 0 to 100 is considered meaningful (50;51). On the basis of the study on early palliative care in advanced lung cancer patients, it can be expected that approximately 80 % of the study participants will still be alive at 12 weeks after inclusion and drop-out for reasons other than death will amount to 15 % [4]. In other words, an overall drop-out rate of 35 % is to be expected, accounting for the planned inclusion of a total of 182 patients in the study.

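### The primary quality-of-life model names only baseline scores; pre-specifying department, ECOG and entry route as covariates would cost almost nothing and may add a little precision

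*Protocol article*

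**What the plan says.** All references are to the protocol article.

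- **Study participants, Table 1, inclusion criterion 2** admits those "within 12 weeks of a new diagnosis of illness progression or patients originating from another hospital who are within 12 weeks of receiving first-line treatment".
- **Table 1, inclusion criterion 4** admits "Patients with an Eastern Cooperative Oncology Group (ECOG) performance status of 0, 1 or 2".
- **Table 1, inclusion criterion 3** restricts prognosis for everyone: "Patients with a life expectancy of approximately one year (assessed by the treating oncologist".
- **Study design** gives one stratification factor: "Stratification will take place for the treating oncology department (Digestive Oncology, Thoracic Oncology and Medical Oncology". The reason given is "in order to prevent imbalances between groups in factors related to possible differences in standard care", which concerns care rather than prognosis.
- **Statistical analysis and sample size calculation** states that "the primary outcome quality of life will be assessed by multivariate regression analyses adjusting for baseline scores". In the next sentence the survival model, for a secondary outcome, is described as "adjusting for demographic and clinical baseline characteristics".
- **Measurement instruments** says that clinical characteristics are collected at baseline from questionnaires and the medical record.

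**The concern.** Patients who have just progressed and patients referred during first-line treatment are at different points in their disease, and ECOG 0 and ECOG 2 describe different functional states. Week-12 quality of life could plausibly differ across these groups even among patients with the same baseline score. Department does not identify either factor, so stratification does not balance them. The article adjusts for clinical factors in a secondary model but names none in the primary one.

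Two things are at stake, both modest. Any variation that these factors explain beyond the baseline score stays in the error term and widens the interval. A chance imbalance in either factor would also shift the primary estimate without correction. Department belongs in the same list: it is the stratification factor, and the usual practice is for the analysis to reflect it.

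**Working it through.** **Inputs from the statistical section.** Difference 12; within-group SD 23.0; 59 per group; power 80%; overall drop-out 35% (20% deaths plus 15% other reasons). The significance level is not stated. Two-sided 0.05 is assumed, because it reproduces the stated number and one-sided 0.05 does not (46 per group by the normal approximation).

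**Step 1: the plan's own figures.** For a two-sample t-test at standardised difference 12/23 = 0.522 and 80% power, the required number is 58.64, so 59 per group and 118 in total. Power at 59 per group is 80.2%. Inflation: 118 / (1 − 0.35) = 181.5, so 182. Both figures reproduce.

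**Step 2: possible gain from the extra covariates.** The documents do not say how much variance they would explain beyond the baseline score, so a range is assumed. With R² the share of residual variance explained, and 23.0 taken as the residual SD before they are added:

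- residual SD = 23 × √(1 − R²)
- noncentrality = 12 / (residual SD × √(2/59))
- interval narrowing = 1 − √(1 − R²)
- equivalent extra evaluable patients = 118 / (1 − R²) − 118

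| Assumed R² | Residual SD | Power | Interval narrower by | Equivalent extra patients |
|---|---|---|---|---|
| 0 | 23.00 | 80.2% | 0% | 0 |
| 0.02 | 22.77 | 81.0% | 1.0% | about 2 |
| 0.05 | 22.42 | 82.2% | 2.5% | about 6 |
| 0.10 | 21.82 | 84.2% | 5.1% | about 13 |

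To give the range a scale, suppose the two routes are split 50:50 and their adjusted week-12 means differ by 10 points. The between-route variance is 0.25 × 10² = 25, and 25/529 = 4.7%. That is a favourable case, since an even split maximises this variance. With a 5-point difference the share is 6.25/529 = 1.2%.

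**Step 3: cost in degrees of freedom.** Department uses 2, ECOG as three categories uses 2, and route uses 1: five in all. Cutting the error degrees of freedom from 115 to 110 at R² = 0 lowers power by about 0.03 percentage points.

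**Step 4: chance imbalance.** For a binary factor of prevalence p that is not stratified, the 95% range of the between-arm difference is ±1.96 × √(2p(1 − p)/m), with m patients per arm. The prevalences are assumed.

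| Prevalence | m = 59 | m = 91 |
|---|---|---|
| 30% | ±17 percentage points | ±13 |
| 50% | ±18 | ±15 |

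At 59 per arm, if the factor's levels differed by 10 points at the same baseline score (assumed), the edge of that range would move the estimate by about 0.17 × 10 = 1.7 to 0.18 × 10 = 1.8 points. The planned difference is 12. A 5-point difference would halve this.

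**The case against.** The strongest case against is that nothing here is wrong. The article is a condensed account and does not say that baseline scores are the only covariates; a fuller list may sit in an analysis plan that is not shown. The survival model differs for a good reason: survival has no baseline value to adjust for, whereas quality of life does, and that value is usually the most useful covariate. The one-year life-expectancy criterion applies to both routes and all ECOG levels and narrows the spread, and the baseline score may absorb much of the rest. The planning SD is a total within-group figure, so this variation is nominally already inside it. Keeping stratification to department is also defensible for 182 patients at one centre.

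Most of this stands, and it limits the point to an optional gain in efficiency. It does not remove the point. The article states the adjustment for both models and the two lists differ, so the suggestion addresses a stated choice.

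Three stronger readings are tempting but unsupported:

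- **That the omission biases the primary estimate.** Randomisation balances these factors in expectation, so leaving them out of a linear model does not bias the treatment comparison.
- **That established prognostic variation is being ignored.** The article reports no association of ECOG or entry route with week-12 quality of life or with death; it is plausible, not documented.
- **That the omission worsens the effect of missing week-12 data.** The article specifies last observation carried forward for all missing values. That rule uses no covariates, so adding these would neither change nor repair it. Whether the rule suits this trial is a separate question.

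**Conclusion.** The point holds as a minor improvement to a stated model. The primary regression names baseline scores but not ECOG, entry route or department. The sample size is correct as stated, and not adjusting does not take power below 80% if the SD of 23.0 holds.

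The gain is about 1 to 4 percentage points of power and a 1% to 5% narrower interval, together with protection against a chance imbalance in ECOG or entry route. These sizes rest on the assumed 2% to 10% of residual variance, two-sided 0.05, and 23.0 standing in for the residual SD. If adjustment for the baseline score already brings the SD below 23.0, power is higher in every row, but the percentage narrowing for a given R² is unchanged. If the true share is near zero, the gain is negligible, and so is the cost.

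**What to change.** In the statistical analysis section, pre-specify that the primary week-12 QLQ-C30 regression includes these fixed covariates beside the baseline score:

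- treating department (three levels, as stratified);
- ECOG (0, 1, 2);
- entry route (progression versus first-line referral).

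Table 1 does not make the two routes mutually exclusive, so state in advance how a referred patient who meets both is coded. If an analysis plan already lists these covariates, confirm that it agrees with the article.

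The cost is a line or two of text and about five degrees of freedom. No new data, visits, patients or stratification factors are needed. The wording should be fixed before outcome data are examined by arm.

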### Data collection

Oncologists will describe the study to the eligible patients with the help of a data manager. The oncologists are asked to use the terms ‘palliative care’ and ‘palliative care team’ specifically while explaining the study, in order for the patient to be thoroughly informed and to avoid confusion when they receive the first visit from the palliative care team. The oncologists will obtain the patient’s written informed consent prior to enrolment. Our researchers will inform the informal caregiver of the patients and obtain written informed consent from them. Study participants will be randomized in a 1:1 fashion to the standard care arm or the intervention arm.

### The intervention

The intervention, primarily led by the palliative care nurse, will consist of four major components: the palliative care consultation, assessment, referring role and training.

#### Palliative care consultation

The intervention consists of systematic consultations with the palliative care nurses of the palliative care team of the Ghent University Hospital shortly after diagnosis of advanced cancer or of the progression of the disease. The palliative care team of the Ghent University Hospital consists of three palliative care nurses (2.5FTE), a palliative care psychologist (0.5FTE) and a palliative care physician (0.5FTE). This systematic early integration of palliative care will be in contrast to standard oncology care, where referral to palliative care is only at the request of physicians, nurses or patients and mostly occurs late in the disease trajectory. The participant receiving systematic early palliative care will meet with the palliative care nurses at least once a month and more if needed or requested by the patient. The palliative care physician will support and advise the palliative care nurses and will have at least one consultation every three months with the participant. All consultations will take place at a time when the patient is at the hospital for diagnostic or therapeutic reasons. The content of the palliative care consultations will be based on the holistic approach of palliative care and will focus on illness understanding and illness perception, symptom burden, psychological coping, spiritual coping and medical decision making by the patient and his or her informal caregiver.

#### Assessment

An interview form (see Additional file 1: Appendix 1) has been developed to aid in the structuring of each consultation and allows for an individual approach with the patient as well as the informal caregiver [4]. The aim of the members of the palliative care team is to comprehensively assess how the patient and informal caregiver present with regard to illness understanding and illness perception, symptom burden, psychological coping, spiritual coping and medical decision-making at every consultation. However, when a participant is not willing to discuss a specific topic, this will be respected. For symptom burden, assessment will not only be performed through personal inquiry based on the time allocation form but also through the use of the Edmonton Symptom Assessment Scale (ESAS) [16]. The different items of the ESAS will be filled out by the patient and will be discussed with the member of the palliative care team. The palliative care nurse or palliative care physician and the patient will systematically consider the previous item scores of the ESAS by using a graph that plots the evolution of the scores. This will provide an overview of the fluctuation of the symptoms over time [16].The palliative care team will report the amount of time spent on these different topics on the interview form.

#### Referring role

Because of their holistic approach to care of the patient, the members of the palliative care team will have an important role in reporting problems that arise during the consultation e.g. debilitating side effects of treatment to the oncology team and other health care professionals involved inside and outside the hospital. To encourage this referring role, the intervention will include regular communication between the members of the palliative care team and other professional caregivers 1) through weekly multidisciplinary meetings with the oncology team; 2) through weekly internal meetings with all the other members of the palliative care team and 3) through reporting in the electronic patient file and the palliative care team is required to complete a referral checklist at the end of every consultation [Additional file 2: Appendix 2] which includes an assessment of the need to contact other professional caregivers such as members of the oncology team, the psychologist, the general practitioner and the home palliative care services.

